**Sample size**

Sample size justification A pilot study showed the mean TFDi in COVID 19 patients on PEEP 5 to be 45%(SD 15); To decrease mean fractional thickening of the diaphragm index by 30% after the dose of morphine with allocation in a 1:1 ratio, 21 patients will be needed in each group. Accounting for dropouts/ loss of data, 25 patients will be recruited in each limb.

*Statistical analysis*

Interim analyses are planned at 50% of sample recruitment, without unblinding to ensure that subjects are not being exposed to an unacceptable level of risk, whether the trial can be stopped early, check some of the assumptions that went into the original design and sample-size calculations of the trial (like within-group variability, recruitment rates, base event rates). The alpha spending strategy used will be one-fifth of the available 5 percent alpha at the interim analysis. i.e., the interim analysis p-value must be < 0.01 to stop the trial early and claim efficacy. Spend the remaining four-fifths of the 5 percent alpha at the end, or the end analysis p-value must be < 0.04 to claim efficacy. The two groups shall be compared for the mean TFdi (overall and 24^th^ hrly) by unpaired t-tests. Within-group comparison of TFdi shall be made (overall and 24^th^ hrly) by Repeated measures analyses.

Secondary outcomes- Intubation, Mortality, duration of mechanical ventilation, ICU stay, Subjective scores, Demographics, and severity of illness shall be compared by chi-square, t-tests, or nonparametric tests as suitable.

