**The interventions**

A baseline assessment of all outcome measures as appropriate will be made. Normal body temperature, RASS of -1 or 0, and VAS < 4 will be ensured by administering Midazolam ( titrated to effect) or Paracetamol as warranted.

All patients will be turned lateral or sitting position, and an injection of LA be given at L2-3 or L3-4 space. An epidural catheter will be inserted under all asepsis and fixed to the skin in the intervention group. It will be fixed firmly with antimicrobial incise drapes covering at least the lower one-third of the back. For patients who appear fidgety, catheter tunneling may also be used.

The control group will have a sham catheter fixed precisely like the intervention group but not entering the epidural space. The fixation and dressing will be similar to the intervention group.

The intervention group will be administered Injection Morphine Sulphate once every 18-24 hours into the epidural space. The doses will be escalated daily (5-10mg), titrated to the effect: escalation limited by hypoventilation resulting in respiratory acidosis (pH <7.2).

The intervention will continue for a minimum of 2 doses and a maximum of 4 doses (96 hours) of morphine. It will be stopped at 120 hours, or if: the epidural catheter gets dislodged before the second dose, the patient is weaned off noninvasive ventilation to high flow mask for a continuous period of 12 hours or requires endotracheal intubation.

The patient will be followed up till death or 28 days after ICU discharge.

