**Respiratory Drive and related parameters**

Once at baseline and once every 8 hours after that, the following will be assessed till the epidural catheter is in situ, or five days whichever is greater.

The researcher will do the baseline assessment, be aware of the group allocation, and insert the epidural catheter (true or sham). She/ He will mark the site of best visualization for USG probe, ensure best fit NIV interface and assess baseline subjective comfort scores.

After that, all assessments will be done by a fixed set of postgraduate ICU trainees, all trained in TFDi assessment but blinded to group allocation.

Ultrasound-guided TFDi- This procedure will be performed as described earlier.(17,19)

The patient will be supine with head-end elevated to 30 %. The right hand will be abducted and kept near the head. The diaphragm will be located by placing the transducer in the intercostal space above the right 8^th^- 11^th^ intercostal space, in the anterior- axillary line, directing the ultrasound beam perpendicular to the diaphragm. The inferior border of the costophrenic sinus will be identified at end-inspiration as the zone of transition from the lung sliding shadow to the visualization of the diaphragm and liver. The zone of apposition will be noted.

The diaphragm thickness will be recorded in time motion (TM) mode.

The sweep speed will be adjusted to obtain a minimum of three to 8 cycles on the same image.

Several diaphragm images (outlined by the two clear, bright parallel lines of the pleural and peritoneal membranes) will be located: the image will be discarded if the two bright lines are not visible. The least and maximum thickness as on eyeballing will be located and a picture stored for subsequent quantitative analysis and crosschecking by a blinded assessor.

The position of the first (baseline) USG assessment will be marked on the skin to allow all subsequent recordings from the same position.

A note will be made of the ongoing sedation dosages and ventilator settings during the measurement of TFdi (settings will be kept the minimum required for patient comfort – but will not be changed/ dictated for purposes of the study)

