**Sample size**

Sample size justification A pilot study showed the mean TFDi in COVID 19 patients on PEEP 5 and clinically optimal pressure support to be 45% (SD 15); To decrease this by 30% at 36 hours after the dose of morphine with allocation in a 1:1 ratio, 21 patients will be needed in each group.

Compliance and missing data- All analyses will be based on the groups as randomly allocated: an intention-to-treat analysis. A per-protocol analysis will also be done. The statistical significance will be taken as the 5% level for the top comparisons and the subsidiary comparisons, the 1% level. Patients with a P/F ratio > 150 at inclusion will be compared to those with lower values.

Data Storage- Because of the unique challenges of repeated data capture in COVID ICU, all repetitive data will be captured photographically and sent to a central data repository online to be categorized and stored by patient name and time of data capture (once every 8 hours), making in 14-time points of data capture for each patient. Data storage will be by blinded personnel.

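### The between-group test of TFdi is an unadjusted t-test that leaves the measured baseline unused; it is valid but gives up precision, and the within-group and P/F comparisons need clearer wording

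*Protocol*

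**What the plan says.** Under Statistical analysis, in the protocol's first Sample size section, the arms are compared as follows: "The two groups shall be compared for the mean TFdi", both overall and 24-hourly, with unpaired t-tests. The next sentence keeps the longitudinal method for a different purpose: "Within-group comparison of TFdi shall be made (overall and 24^th^ hrly) by Repeated measures analyses".

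Baseline values are collected. The section on the interventions states: "A baseline assessment of all outcome measures as appropriate will be made". The section Respiratory Drive and related parameters sets the TFdi schedule: "Once at baseline and once every 8 hours after that". The protocol nowhere enters the baseline as a covariate or in a change score for the comparison between arms.

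The second Sample size section, under Detailed methodology, adds in its paragraph on compliance and missing data: "Patients with a P/F ratio > 150 at inclusion will be compared to those with lower values". It names no outcome, no treatment contrast within each stratum and no interaction.

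**The concern.** The trial is small, with 21 patients per arm needed and 25 recruited, and its outcome varies widely between patients. In that setting the baseline of the same measurement is usually the most useful covariate available, and here it is already collected. Leaving it out makes the standard error of the treatment effect larger than it need be whenever baseline and follow-up are correlated. It also leaves any chance difference between the arms at baseline uncorrected.

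Two neighbouring sentences add to this. The repeated-measures analysis is confined to change within each arm, which is not a randomised comparison: both arms receive NIV optimisation and sedation and may change for reasons unrelated to morphine. The P/F sentence, read literally, contrasts less hypoxaemic with more hypoxaemic patients. That describes prognosis and does not show whether the effect of morphine differs between them.

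**Working it through.** **Inputs from the protocol.** Mean TFdi 45%, SD 15; target decrease 30%; 21 per arm needed, 25 recruited; final p-value threshold 0.04. Read as relative, the decrease is 0.30 × 45 = 13.5 points, a standardised effect of 13.5/15 = 0.90.

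**Assumptions.** Two-sided testing and 80% power, neither of which is stated; equal SDs at baseline and follow-up; a baseline-outcome correlation r, which the documents do not give.

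**Step 1: reproduce the stated sample size.** For a two-sample t-test with d = 0.90, two-sided 5% and 80% power, the exact solution is 20.4, so 21 per arm. This agrees with the protocol. At alpha 0.04 it is 21.8, so 22. Reading the decrease as 30 absolute points gives only 4 to 8 per arm (two-sided alpha 0.05 to 0.01, 80% power) and does not reproduce. The design therefore matches an unadjusted comparison and takes no credit for baseline.

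**Step 2: effect of baseline adjustment.** The residual SD is 15 × √(1 − r²), and the variance falls by the fraction r². The effective standardised difference is 0.90/√(1 − r²). Power is from the t distribution at two-sided alpha 0.04:

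| r (assumed) | Variance cut | Residual SD | Power, 21 per arm | Power, 25 per arm |
|---|---|---|---|---|
| 0 (t-test) | 0% | 15.0 | 78% | 85% |
| 0.1 | 1% | 14.9 | 79% | 86% |
| 0.2 | 4% | 14.7 | 80% | 87% |
| 0.3 | 9% | 14.3 | 82% | 89% |
| 0.5 | 25% | 13.0 | 89% | 94% |
| 0.7 | 49% | 10.7 | 97% | 99% |

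Charging one degree of freedom for the covariate changes each power by less than 0.1 percentage point.

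**Step 3: chance imbalance at baseline.** Its standard error is 15 × √(2/25) = 4.2 points at 25 per arm and 15 × √(2/21) = 4.6 at 21 per arm, about a third of the 13.5-point target. With equal SDs, an imbalance reaches the follow-up comparison multiplied by r. A 4-point imbalance therefore shifts the expected result by 1.2, 2.0 or 2.8 points at r = 0.3, 0.5 or 0.7.

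**Step 4: change score as an alternative.** Its SD is 15 × √(2(1 − r)): 17.7 at r = 0.3, 15.0 at r = 0.5 and 11.6 at r = 0.7. Below r = 0.5 it is worse than the raw value, and at each of these r it is worse than ANCOVA.

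**Step 5: arm-by-P/F interaction.** Assume 25 per arm, a 50:50 split at P/F 150 and no baseline adjustment. The standard error is 15 × √(2/12.5 + 2/12.5) = 8.5 points. For an interaction as large as the whole 13.5-point effect, power is about 36% at the 5% level and 16% at the 1% level that the protocol sets for subsidiary comparisons. The smallest interaction detectable with 80% power at 5% is (1.96 + 0.84) × 8.5, about 24 points.

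**The case against.** The strongest reply is that nothing here is an error of inference. The t-test is unbiased under randomisation, its standard error already includes chance baseline variation, and it is the test that reproduces the stated 21 per arm. All of that stands. A reader might infer that the primary test is invalid, or that a baseline imbalance passes in full into the result. The documents support neither: type I error is unaffected, and an imbalance carries over only in proportion to the correlation.

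The size of the gain is also uncertain. Morphine is titrated to effect, which could weaken the link between baseline and outcome in the active arm, and at r of 0.2 or less little is gained. This stands as a limit on the magnitude.

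The baseline has a weakness of its own. The section Respiratory Drive and related parameters has it assessed by a researcher described as aware of allocation, while later readings are made by blinded trainees. An allocation-related error in the baseline would enter an adjusted estimate but not a t-test on follow-up values. The same section stores images for quantitative analysis by a blinded assessor. That reduces the problem, though it cannot remove bias in how the images were acquired.

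A reader might also infer that the within-group tests are meant as proof of efficacy. The protocol does not say so: it specifies the between-group test separately and frames its objectives as comparisons between the two groups. Likewise the P/F sentence may be loose wording for an ordinary subgroup analysis.

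**Conclusion.** The concern holds as one of efficiency and clarity, not of validity. The protocol fixes an unadjusted between-group test while collecting a baseline that could sharpen it at almost no cost. At assumed correlations of 0.3 to 0.7, power at 21 per arm and alpha 0.04 would be 82% to 97% instead of 78%; at 25 per arm, 89% to 99% instead of 85%. These figures rest on the pilot SD applying at both times, a 13.5-point effect, two-sided testing and a correlation that the documents do not supply.

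The adjustment cannot be specified until one primary time point or summary is named. The statistical analysis tests overall and 24-hourly means, whereas the second Sample size section sizes the trial on TFdi at 36 hours, and 36 is a multiple of neither 24 nor the 8-hour measurement interval.

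The P/F sentence does not, as worded, ask whether the treatment effect differs. With 50 patients, even the correctly worded question could only be exploratory.

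**What to change.** 1. Name one primary TFdi time point or summary, reconciling the overall and 24-hourly means with the 36 hours used for the sample size.
2. Replace the between-group t-test by an ANCOVA of that outcome on arm and baseline TFdi. A mixed model over the repeated readings is an alternative if its covariance structure is parsimonious: with 13 follow-up times an unstructured matrix has 13 × 14/2 = 91 parameters, for at most 50 patients.
3. Take the covariate from the blinded reading of the stored baseline images, and state whether the baseline scan is acquired before or after allocation is known.
4. Label the within-group repeated-measures tests as descriptive.
5. Reword the P/F comparison as an exploratory arm-by-P/F interaction with the treatment effect and its confidence interval in each stratum, and state its low power.

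The cost is one degree of freedom and a change of wording. No extra patients, visits or measurements are needed.

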**The research question**

Aim To compare the TFDi (primary endpoint), ventilator parameters, subjective comfort, rate of intubation, length of mechanical ventilation, length of ICU stay, and mortality of moderate to severe COVID 19 patients on noninvasive ventilation (NIV), with and without epidural morphine.

*Objectives*

To compare-

Thickening Fraction index of diaphragm TFdi, surrogate for the respiratory drive (primary outcome measure)

P0.1, mechanical ventilation (MV), respiratory rate (RR), Tidal volume (Vt), subjective comfort, the dose of sedatives needed, Visual Assessment of Pain (VAS), Richmond Agitation and Sedation Scores (RASS), time to intubation, length of mechanical ventilation, the incidence of VAP, incidence of sepsis, COVID 19 markers, length of stay in ICU, length of stay in hospital and mortality between the two groups.

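### The primary between-group TFdi test leaves out the baseline TFdi that the protocol plans for every patient; the test is valid but gives up precision

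*Protocol*

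**What the plan says.** The protocol names TFdi as the primary outcome (The research question, Objectives). For the comparison between arms, the Statistical analysis text under Sample size states: "The two groups shall be compared for the mean TFdi (overall and 24^th^ hrly) by unpaired t-tests". No covariate, change score or mixed model is named for that contrast. The next sentence reads "Within-group comparison of TFdi shall be made (overall and 24^th^ hrly) by Repeated measures analyses", so the repeated-measures analysis runs inside each arm and does not estimate the effect of morphine against sham.

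Baseline TFdi is planned in two places. The interventions section says "A baseline assessment of all outcome measures as appropriate will be made". The section Respiratory Drive and related parameters, which covers TFdi, says "Once at baseline and once every 8 hours after that, the following will be assessed". The same section says who takes that first reading: "The researcher will do the baseline assessment, be aware of the group allocation, and insert the epidural catheter (true or sham".

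Nothing else in the protocol brings baseline TFdi into the contrast. Allocation follows a random numbers list, with no stratification described. Demographics and severity are compared between arms, and patients above and below a P/F ratio of 150 are compared, but neither step adjusts the TFdi estimate.

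**The concern.** TFdi varies widely between patients: the pilot figures are a mean of 45% and an SD of 15. Part of that variation is already present before treatment, and the trial measures it. A test on follow-up means alone leaves it in the residual, so the standard error is larger than necessary whenever baseline and follow-up are correlated. In a trial of 50 patients the arms will also differ somewhat at baseline by chance, and a share of that difference stays in the unadjusted estimate.

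This is not a detail left to an analysis plan that is not shown, because the protocol itself fixes the method for the primary endpoint. At stake are the width of the confidence interval and the power of the primary comparison, in a single-centre trial that asks severely ill patients to accept an invasive or sham procedure.

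**Working it through.** **Inputs from the protocol.** Mean 45 and SD 15; relative reduction 30%, so the difference is 0.30 × 45 = 13.5 points; allocation 1:1; 21 evaluable and 25 recruited per arm (Sample size). Final significance level 0.04 (Statistical analysis), and general level 5% (second Sample size section).

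**Assumed, because not stated.** Two-sided testing, 80% target power, and a baseline to follow-up correlation r of 0.3, 0.5 or 0.7, with r = 0 as the worst case.

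**Step 1: reproduce the stated sample size.** The standardised difference is 13.5/15 = 0.90. The normal approximation gives n = 2 × (1.960 + 0.842)² / 0.90² = 19.4, so 20 per arm. The exact noncentral-t calculation for an unpaired t-test gives 79.2% power with 20 and 81.2% with 21, so 21 per arm. This matches the protocol: the trial is sized on the unadjusted test.

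**Step 2: unadjusted power.** The standard error is 15 × √(2/n): 4.63 with 21 per arm and 4.24 with 25. With 2n − 2 degrees of freedom, power is 81.2% (5% level) and 78.4% (4% level) with 21, and 87.7% and 85.5% with 25.

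**Step 3: power with baseline as covariate.** The residual SD is 15 × √(1 − r²), with 2n − 3 degrees of freedom. Estimating the covariate slope inflates the variance on average by 1 + 1/(2n − 4), that is 1.026 with 21 per arm and 1.022 with 25. The standard error is therefore 15 × √(1 − r²) × √(2/n) × √(1 + 1/(2n − 4)).

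| r (assumed) | SE, 21 per arm | Power 5% / 4%, 21 per arm | SE, 25 per arm | Power 5% / 4%, 25 per arm |
|---|---|---|---|---|
| unadjusted t-test | 4.63 | 81.2 / 78.4% | 4.24 | 87.7 / 85.5% |
| 0 | 4.69 | 80.2 / 77.2% | 4.29 | 86.9 / 84.7% |
| 0.3 | 4.47 | 83.7 / 81.1% | 4.09 | 89.8 / 87.9% |
| 0.5 | 4.06 | 90.0 / 88.1% | 3.71 | 94.5 / 93.3% |
| 0.7 | 3.35 | 97.6 / 96.9% | 3.06 | 99.1 / 98.8% |

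A 20,000-run simulation with 21 per arm gave 83.9/81.2%, 90.1/88.1% and 97.4/96.8% for r = 0.3, 0.5 and 0.7, in agreement with the formula.

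**Step 4: validity.** With no true effect and 21 per arm, 4,000 simulated trials per setting gave rejection rates of 4.6% to 5.9% for the t-test and 4.5% to 5.6% for the adjusted model at the nominal 5% level. Both hold their level.

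**Step 5: chance imbalance.** If the baseline SD is also 15, the chance difference in baseline means has a standard error of 4.63 points with 21 per arm and 4.24 with 25. Only r times that difference enters the unadjusted estimate. With 25 per arm, a one-standard-error imbalance moves it by 1.3, 2.1 or 3.0 points at r = 0.3, 0.5 or 0.7, against a target of 13.5.

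**The case against.** The strongest reply is that nothing here is an error. Randomisation makes the unpaired t-test unbiased, its type I error is held, and the sample size was worked out for exactly this test. That stands.

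The size of the gain is also unknown. Entry is restricted to patients with high drive, later readings are taken at whatever ventilator support is in use, and baseline and follow-up are measured by different people. Each of these could lower r, and at r = 0.3 the gain is only about 2 to 3 points of power. Averaging many follow-up readings in the overall mean could raise r, so the size is open in both directions. This stands too, and it is why the result is shown as a range.

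The remedy has a weak spot. The baseline is taken by a researcher who knows the allocation, and a covariate that can be influenced after allocation could introduce bias that the t-test does not have. A blinded re-reading of the stored image only partly answers this, because the same operator marks the probe site and acquires the image. Taking the baseline before allocation is revealed answers it properly.

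A reader might infer more than the documents support:
- **The primary result would be biased, or the test invalid.** It would not; the t-test's standard error already includes the chance baseline variation, so imbalance is not a second harm on top of the lost precision.
- **A baseline gap passes whole into the morphine effect.** Only r times the gap does.
- **The trial is underpowered.** Power falls below 80% only at the 4% level and only if the whole dropout allowance is used up; with 25 evaluable per arm it is 85.5%.
- **P0.1, respiratory rate, tidal volume and minute ventilation share the fault.** The t-test sentence covers TFdi alone, and no test is fixed for those variables.

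**Conclusion.** The point holds as a loss of precision in the stated primary analysis. With 21 evaluable patients per arm, baseline adjustment would raise power at the 4% final level from 78.4% to between 81.1% and 96.9%; with 25 it would rise from 85.5% to between 87.9% and 98.8%. If baseline and follow-up were uncorrelated, adjustment would cost about 1 point.

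These figures rest on the protocol's difference of 13.5 and SD of 15, on two-sided testing, and on assumed correlations of 0.3 to 0.7. The direction is secure for any appreciable correlation; the size is not known from the document. The sample size needs no correction, and the finding is limited to TFdi.

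**What to change.** In the Statistical analysis text, replace the between-group unpaired t-test of TFdi with a linear model of post-baseline TFdi on arm, with baseline TFdi as covariate. Apply it to the overall mean, stating that the baseline reading is excluded from that mean, and to each 24-hourly value. Keep the unpaired t-test as a sensitivity analysis.

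In Respiratory Drive and related parameters, have baseline TFdi recorded before allocation is revealed. If that is not feasible, use the blinded assessor's reading of the stored baseline image as the covariate. Because images without two visible lines are discarded, add a short rule for a missing baseline value.

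The cost is a few sentences of wording, one degree of freedom and possibly a change in the order of two bedside steps. No new measurements and no extra patients are needed.

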**Trial population**

Trial site(s) and population(s)- COVID ICU patients in AIIMS Bhubaneswar

Inclusion and exclusion criteria- Include- Adult patients with COVID 19 pneumonia 18-80 years of age. Requiring NIV to maintain oxygenation.

Exclusion criteria- Metabolic acidosis HCO3-< 16 or pH < 7.2. Severe hypoxemia warranting cessation of NIV and intubation, non-acceptance of NIV. Chronic opioid user. Uncontrolled sepsis, end of life (EOL) orders.

Sources or methods of recruitment- Daily discussion at 8 am of new admissions to COVID ICU on NIV – assessment for high respiratory drive despite Spo2 > 90 and adequate NIV support

Information for participants- PIS will be provided. Written informed consent will be taken for the patient/ kin of all eligible patients.

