**Outcome assessment**

*Outcome measures*

TFdi, p0.1, MV, RR, Vt (average of 3 readings, ^eighth^ hourly )

Arterial blood gas and associated values-Pa o2, PaCO2, pH, HCO3, p/F ratio (at least once a day)

Spo2, Fio2, ROX index, Subjective comfort and dyspnea scores – 8^th^ Hourly

VAS, RASS, Weaning (hours off NIV on high flow mask or face mask)- (mean values over 24 hours)

Intubation- Yes/ No: Days after randomization

Length of stay in ICU

Outcome at 28 days of admission

Incidence of excessive respiratory depression (PaCO2> 45 and pH < 7.2)

Incidence of difficult/ failed epidural insertion, catheter pullouts, and complications such as bleeding/ infection/ hematoma will be documented.

Timing of outcome assessment- - Every 8^th^-hour assessment / daily / one time as detailed above

Blinding- The assessor, patient, nurses, physicians, and treating team will be blind to group allocation. One member of the team not involved in research will administer the drug.

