**Reassess Minute volume after 30 minutes.**

- Exclusion: PaCO2 ≥ 45 mmHg *and* pH < 7.2; Compensated respiratory acidosis was accepted up to a pH 7.2 according to standard ARDS lung-protective ventilation guidelines *if GCS >12*

Compensated metabolic acidosis with HCO3 < 16mmol/l with sepsis/ acute or chronic renal failure,

Hemodynamic instability (MAP< 65 mmHg) *and* need of increasing doses of vasopressors in last 6 hrs.; GCS <12;

Contraindication to noninvasive ventilation;

Urgent need for intubation (evaluated by the clinician in charge)

Refusal to participate or participate in another study.

Do-not-intubate decision

Epidural catheter block/ dislodged/ less than two doses of the drug could be administered.

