**Intubation and mortality rates,**

Duration of NIV and invasive mechanical ventilation

Cause for conversion to IMV- Progressive respiratory failure/ New Sepsis/ Neurologic dysfunction/ Hemodynamic instability

The length of ICU-stay,

The organ dysfunctions and adverse events, including cardiac dysrhythmia, septic shock, and cardiac arrest, will be recorded until the ICU stay.

Mortality will be followed today 28.

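### Intubation is compared apart from mortality, so by default a death on NIV without intubation counts as not intubated; add intubation-or-death beside it

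*Protocol*

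**What the plan says.** Under Outcome assessment, the protocol records "Intubation- Yes/ No: Days after randomization", so both the event and its day are collected. The research question section lists "time to intubation, length of mechanical ventilation, the incidence of VAP" among the objectives. The detailed methodology lists "Intubation and mortality rates" as data to collect and says "Mortality will be followed today 28".

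For analysis, the Sample size section (statistical analysis paragraph) names "Secondary outcomes- Intubation, Mortality, duration of mechanical ventilation, ICU stay, Subjective scores" and continues: "Demographics, and severity of illness shall be compared by chi-square, t-tests, or nonparametric tests as suitable". The second Sample size section, in the detailed methodology, sets intention to treat for all analyses, adds a per-protocol analysis, and sets 5% for the main comparisons and 1% for subsidiary ones.

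Two entry exclusions bear on the point: "Uncontrolled sepsis, end of life (EOL) orders" under Trial population and "Do-not-intubate decision" in the detailed exclusion list. A separate section gives predefined criteria for endotracheal intubation.

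The protocol does not say how a patient who dies without intubation is scored. It defines no combined outcome of intubation and death.

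**The concern.** Death on NIV makes later intubation impossible. If the patient then counts as not intubated, the worst result and a good result (weaned and alive) share one category. An arm with more such deaths shows a lower intubation rate for a reason unrelated to avoided respiratory failure.

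The balance could differ by arm in this trial. The introduction says opioids ease dyspnoea by altering perception and reducing drive. Two of the intubation criteria, a high respiratory rate and lack of improvement in subjective scores, are measures the drug is meant to change. Arms with the same course of lung failure could therefore reach intubation at different rates. This bears only on interpreting the outcome and is no comment on the clinical criteria.

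At stake is the reading of a stated aim, the rate of intubation.

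**Working it through.** **1. The arm size.** The protocol gives no planning figure for intubation, so the only figure to reproduce is the sample size for the primary outcome (TFdi).
- Inputs: mean 45%, SD 15 and a 30% relative decrease, so the difference is 0.30 × 45 = 13.5 points and the standardised difference is 13.5/15 = 0.9. Power is not stated; I assume 80% with two-sided 5%.
- n = 2(1.960 + 0.842)² / 0.9² = 19.4, so 20 per group by normal approximation. The t-test version gives 20.39, rounded up to 21, which matches the protocol.
- 21/25 = 0.84, so 25 per arm allows for 16% loss. I use 25 per arm below.

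**2. How the death is scored.** A Yes/No item, all randomised patients in the denominator and no rule for death give a default of No. Of the tests listed, chi-square is the one that fits a Yes/No item.

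**3. Effect of one such death.** 1/25 = 4 percentage points off that arm's intubation rate.

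**4. An illustration.** The protocol gives no event rates, so these are assumptions.

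| | Control | Morphine |
|---|---|---|
| Intubated | 50% | 40% |
| Died without intubation | 5% | 15% |
| Either | 55% | 55% |

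- SE of the intubation difference = √(0.50×0.50/25 + 0.40×0.60/25) = √0.0196 = 14 points. The apparent benefit is 10/14 = 0.71 SE.
- With 40% vs 30% intubated, SE = √(0.40×0.60/25 + 0.30×0.70/25) = √0.018 = 13.4 points, and the same 10 points are 0.75 SE.
- Swapping the arms reverses the sign.

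**5. How many excess deaths would give a false significant result.** Suppose each arm has the same number of failures (intubated, or dead without intubation), and k more of them in one arm are deaths without intubation. Pearson chi-square, no continuity correction, 25 per arm:

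| Failures per arm | k | Intubated | p |
|---|---|---|---|
| 12 | 2 | 40% vs 48% | 0.57 |
| 12 | 4 | 32% vs 48% | 0.25 |
| 12 | 7 | 20% vs 48% | 0.037 |
| 12 | 8 | 16% vs 48% | 0.015 |
| 10 | 8 | 8% vs 40% | 0.008 |
| 15 | 8 | 28% vs 60% | 0.023 |

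The combined outcome is identical in the two arms in every row (p = 1.0). Of the rows shown, only 10 failures with k = 8 passes the 1% level. With k = 9, chi-square is 50 × 225²/(25×25×15×35) = 7.71 for 12 failures and 50 × 225²/(25×25×21×29) = 6.65 for 15, both just above the 1% critical value of 6.63. So 8 or 9 excess deaths are needed.

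**6. Allowing for chance.** With an assumed 50% failure rate in both arms, exact enumeration gives the probability of a significant intubation result favouring the arm with more unintubated deaths:

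| Excess unintubated deaths | 5% level | 1% level |
|---|---|---|
| 0 points | 3% | 0.5% |
| 8 points | 10% | 2% |
| 16 points | 24% | 8% |
| 24 points | 45% | 21% |

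**The case against.** The strongest reply is that the protocol is less rigid, and better protected, than a quick reading suggests.

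- A reader might infer that intubation is fixed as a bare proportion tested by chi-square. The documents do not support that: the day of intubation is recorded, time to intubation is an objective, and chi-square sits in a list to be used as suitable. This stands. Scoring a death as No is the default that follows from the text, not a written rule.
- A rule for such deaths might belong in the statistical analysis plan, which is not shown. This stands in part. Silence alone would be no finding. But the protocol itself sets the Yes/No item, the separate comparison and the family of tests, and a plan that followed these would inherit the problem.
- Exclusion of do-not-intubate and end-of-life patients, predefined intubation criteria and a blinded treating team all make unintubated deaths fewer and less likely to depend on arm. This stands, but the exclusions act only at entry, and none of these rules out a later decision or a sudden death.
- Mortality is compared beside intubation. True, but two separate tables do not show which deaths occurred without intubation.
- A reader might infer that morphine will appear to prevent intubation because of hidden deaths. The protocol gives no rates and no evidence of direction, so the distortion could favour either arm.
- A reader might also worry about Kaplan-Meier estimates with deaths censored. The protocol proposes no such analysis.

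**Conclusion.** The point holds as a weakness of a secondary comparison. Followed as written, the intubation comparison puts deaths on NIV without intubation together with successful weaning, at 4 points per excess death in an arm of 25. In the illustration that is a 10-point difference, 0.71 to 0.75 SE, with no difference in failure.

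The stronger reading, that the trial is likely to declare a false intubation benefit, is not supported. If intubation falls under the 1% level for subsidiary comparisons, which is my reading, about 8 excess unintubated deaths would be needed when failures are equal. An excess of 8 points (2 patients in 25) raises the chance of a false result in that direction only from 0.5% to 2%. The harm is mainly to the point estimate and its interpretation.

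The conclusion rests on the default scoring in the absence of a rule, on intention to treat governing the denominator, and on assumed event rates. The primary outcome is not affected.

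**What to change.** In the statistical analysis paragraph, keep the intubation proportion and add text such as:

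*Intubation or death without intubation within 28 days of randomisation will be compared between arms in all randomised patients. The numbers intubated, dead without intubation, and alive without intubation will be shown by arm. Any difference in intubation will be read together with this comparison.*

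The time origin must be stated. The protocol counts 28 days from ICU discharge in The interventions and from admission in Outcome assessment, and gives no origin where it sets mortality follow-up.

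The cost is small. Day of intubation and day-28 mortality are already collected, so the change is mainly wording; vital status must be known to 28 days from randomisation, which the follow-up to 28 days after ICU discharge covers. The downside is that the combined outcome is less specific to intubation and gives intubation and death equal weight. For that reason it stands beside the intubation proportion instead of replacing it, with the components shown.
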